#### Proteomic analysis of blood samples

2.4.2

Following data acquisition, proteomic data is processed using sophisticated bioinformatics software, encompassing peptide identification, protein inference, and quantitative analysis. Initially, raw mass spectrometry data is analyzed to identify peptides. Algorithms such as Mascot, Sequest, or MaxQuant will be employed to enhance accuracy and sensitivity in identifying peptides with high confidence. Then comes the protein inference, where the identified peptides are mapped back to their corresponding proteins, using probabilistic models. After that, quantitative analysis is performed to measure the abundance of proteins in the samples. Techniques such as label-free quantification, tandem mass tags (TMT), or isobaric tags for relative and absolute quantitation (iTRAQ) may be utilized. This approach is employed to delineate alterations in the blood proteome, thereby enhancing our understanding of the biological responses to health, disease states, and environmental stimuli.

#### Blood metabolomics analysis

2.4.3

The mass spectrometry-derived data is subjected to bioinformatics processing, including the identification and quantification of spectral peaks, normalization, and correlation with a comprehensive database of known metabolites. Advanced algorithms are utilized to detect and identify spectral peaks within the mass spectrometry data. Once the peaks are identified, quantification is performed to measure the concentration of each metabolite. To account for variations in sample preparation and instrument sensitivity, normalization techniques are applied. The identified metabolites are then correlated with a comprehensive database of known metabolites. After these processing steps, statistical analysis and data visualization techniques are employed to compare the metabolite profiles and concentrations under varying conditions, thereby elucidating the impact of hypoxia on physiological function.

#### Fecal and oral metagenomic analyses

2.4.4

The raw sequencing data obtained is meticulously quality-controlled to exclude sequences of low quality and those not of microbial origin. Subsequent to this, sequence assembly, operational taxonomic unit (OTU) clustering, and species annotation are executed using advanced bioinformatics tools, such as QIIME or Mothur. A detailed examination of the microbial community structure and function is conducted through a series of analyses, including diversity assessments using metrics like Shannon and Simpson indices, species abundance statistics, and functional prediction, thereby providing insights into the correlation between gut microbiota and the health status of the host.

#### Fecal metabolomics analysis

2.4.5

The spectroscopic data from fecal metabolomics undergoes thorough processing using advanced bioinformatics software. This begins with peak detection. Following peak detection, metabolites are identified and quantified by comparing detected peaks against established databases, such as the Human Metabolome Database (HMDB). Normalization techniques are applied to standardize the data, addressing variations from sample preparation and analytical conditions. By comparing metabolite signatures across different samples, this approach aims to identify metabolic shifts linked to hypoxic conditions. Such analysis provides insights into how the host’s metabolism adapts to low oxygen levels. Moreover, it highlights the interplay between the host and gut microbiome, as metabolites produced by microbial metabolism can significantly influence host physiology.

#### Multi-omics analysis of blood, stool and oral samples

2.4.6

Finally, a comprehensive bioinformatics framework is established for integrating and analyzing multi-omics data from blood, fecal, and oral samples. This integrative approach combines genomic, proteomic, metabolomic, and metagenomic data to provide a holistic understanding of biological systems.

The process begins with data harmonization to standardize different omics datasets, ensuring compatibility for analysis. Advanced statistical methods and machine learning algorithms are then employed to identify cross-omics patterns and correlations. Techniques like principal component analysis (PCA) and clustering help reveal significant trends and relationships.

Network analysis further elucidates interactions between biological molecules, allowing researchers to visualize complex relationships among genes, proteins, and metabolites. This helps identify key hubs and pathways involved in the acclimatization of Tibetan individuals to the hypoxic plateau environment.

### Statistical analysis of detection indicators

2.5

SPSS V.26.0 will be used as the statistical software. Quantitative data with a normal distribution will be presented as means with standard deviations and will be compared between groups with the use of Student’s t-test or the rank-sum test. Quantitative data that do not follow a normal distribution or homogeneity of variance will be presented as median and IQR, and comparisons between groups will be performed by the Mann–Whitney U test. Enumeration data will be presented as ratios and percentages, and χ^2^ tests will be used for comparison. Two-tailed *p* < 0.05 is considered statistically significant.

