### Design

2.1

This study is a single-center prospective observational study. It is intended to employ a suite of physiological and medical instruments in conjunction with internationally recognized standardized physiological and psychological questionnaires to dynamically monitor the physiological and psychological acclimatization of medical professionals from Peking Union Medical College Hospital. The monitoring will be conducted at seven key time points: prior to departure from Beijing, within 1–7 days post-arrival in Tibet during the acute phase of plateau hypoxia stress, during 2-week, 3-month, 6-month, and 12-month stays in Tibet during the chronic phase of plateau hypoxia stress, and upon return to Beijing.

The physiological parameters to be assessed include blood pressure, heart rate, fingertip venous oxygen saturation, hemoglobin concentration, hematocrit, physical phenotype, electrocardiogram conduction, cardiovascular function, and pulmonary function. Concurrently, questionnaires will be administered to assess acute mountain sickness, sleep quality, and emotional state. Blood, fecal, oral, and urine samples will be collected for further analysis, encompassing blood biochemical measurements, blood leukocyte whole gene expression profiling, blood proteomics, blood metabolomics, fecal metagenomics, fecal metabolomics, oral microbiota metagenomics high-throughput sequencing, and urine microprotein detection. Additionally, fundus examination and a six-minute walk test will be conducted.

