### Study population

2.2

The study will recruit 17 eligible medical professionals from Peking Union Medical College Hospital who are qualified to support Tibet and meet the basic requirements for physical examination, with a gender distribution of 10 males and 7 females. Participants must be between the ages of 20 and 65 years, able to provide written informed consent, and willing to cooperate. The inclusion and exclusion criteria will be strictly adhered to, ensuring the integrity and relevance of the sample.

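### Section 2.5 puts the same rank test in both the normal and the non-normal branch, gives no criterion for choosing a test for normal data, and does not hold one summary per indicator across the seven visits (minor)

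*Protocol article*

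**What the plan says.** Section 2.5 (Statistical analysis of detection indicators) gives a two-branch rule for quantitative indicators.

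- **Normal branch.** Summary: "Quantitative data with a normal distribution will be presented as means with standard deviations". Test: these data "will be compared between groups with the use of Student’s t-test or the rank-sum test".
- **Other branch.** Summary: "Quantitative data that do not follow a normal distribution or homogeneity of variance will be presented as median and IQR". Test: "comparisons between groups will be performed by the Mann–Whitney U test".

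A two-tailed p below 0.05 "is considered statistically significant". The section does not say how normality is judged, or whether that is done per visit, per compared group or once per indicator.

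Two design facts matter here. Section 2.1 (Design): "The monitoring will be conducted at seven key time points". Section 2.2 (Study population): "The study will recruit 17 eligible medical professionals from Peking Union Medical College Hospital", of whom 10 are men and 7 are women.

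**The concern.** The rule has two defects.

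1. **The branches overlap.** The two-sample rank-sum test and the Mann–Whitney U test are one procedure under two names. The rule appears to separate normal from non-normal data, yet it allows the same test for both. Within the normal branch it offers two tests and no way to choose, so the choice can be made after both p-values are known.
2. **The data choose the summary.** The aim is to follow each indicator over seven visits. With at most 17 values per visit, a normality check is a noisy decision. Nothing in section 2.5 requires an indicator summarised as a mean at one visit to be summarised the same way at the next. Equal variance is also a property of a comparison rather than of an indicator, so the summary could depend on which sets are being compared.

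At stake is whether the descriptive course of an indicator from Beijing to Tibet and back can be read along one line. For a skewed marker, a mean at one visit and a median at the next differ even when nothing has changed. Pairing is a separate question: the same switching could occur between a paired t-test and a signed-rank test.

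**Working it through.** The plan gives no error rate or other figure for this rule, so there is nothing to reproduce.

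**Inputs from the article:** 17 participants (10 men, 7 women); seven visits; two-sided 0.05; the two-branch rule.

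**Assumptions, because the article gives no figures:** Shapiro–Wilk at 5% applied separately at each visit; no missing values; between-visit correlation 0.5 to 0.8; indicators either normal or log-normal with log-SD 0.3, 0.5 or 0.8.

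**Step 1: are the two rank tests the same?** On one simulated data set of 10 v 7, the rank-sum and Mann–Whitney tests (normal approximation, no continuity correction) both gave p = 0.09711. They are the same test.

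**Step 2: how often would summaries be mixed?** For a truly normal indicator and independent visits, the chance that at least one of seven checks fails is 1 − 0.95^7 = 1 − 0.698 = 0.302. The chance that all seven fail is negligible, so this is also the chance of a mixture. Simulation of 17 people at seven visits, counting runs in which some but not all visits fail:

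| True distribution | Mixed mean/median, correlation 0.5 to 0.8 |
|---|---|
| Normal | 25–30% |
| Log-normal, log-SD 0.3 | 59–77% |
| Log-normal, log-SD 0.5 | 79–95% |
| Log-normal, log-SD 0.8 | 65–81% |

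The share falls again at strong skew because most visits then fail together. If normality is judged once per indicator, the share is 0 by construction.

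**Step 3: how large is the descriptive gap?** For an unchanged log-normal marker, mean/median = exp(σ²/2):

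- σ = 0.3: exp(0.045) = 1.046
- σ = 0.5: exp(0.125) = 1.133
- σ = 0.8: exp(0.320) = 1.377

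These are population ratios. Under the rule, a visit shown as a mean has first passed the normality check. With that condition, the mean at passing visits exceeds the median at failing visits by about 8–9%, 15–16% and 26–27%. The conditional figures are the relevant ones.

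**Step 4: what does the free choice of test cost?** Normal data, no true difference, smaller of the two p-values always reported:

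| Comparison | False-positive rate |
|---|---|
| Different people, 10 v 7 | 5.7–6.0% |
| Different people, 9 v 8 | 5.8% |
| Same 17 people at two visits, correlation 0.5 | 1.1% |
| Same 17 people at two visits, correlation 0.8 | 0.06% |

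A t-test chosen in advance gave 5.1% at 10 v 7. The excess in comparisons of different people is therefore under one percentage point. For the same people at two visits there is none: independent-group tests ignore the correlation and are very conservative.

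**The case against.** The strongest reply is that choosing mean (SD) or median (IQR) by distribution is a common convention, and that how normality is checked is a detail a condensed article may leave to the full protocol or analysis plan. This has force. A reader might infer that the rule is to be applied at each visit. The text neither says so nor excludes it, so switching between visits is permitted rather than prescribed, and the mixing percentages depend on that reading.

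A reader might also infer that the free choice of test inflates false positives in the main comparisons over time. The documents do not support that. With 17 participants, a 17 v 17 comparison can only be the same people at two visits, and there the rate is about 1% or less at the assumed correlations.

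A third tempting reading is that mixed summaries would produce false significance. They would not: no test in section 2.5 compares a mean with a median, and the two summaries carry different labels. The harm is confined to description.

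Finally, no passage gives the distribution of any marker, so skewness in the concentrations is an expectation and not a documented fact.

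What the reply does not remove is the wording that is there. The article states a rule, and that rule names one rank test in both branches, gives normal data two tests with no criterion, and ties the summary to the observed data. An unseen plan that repeats the rule repeats the defect; one that differs from it contradicts the article.

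**Conclusion.** The concern holds as a minor one. The overlap of the two branches and the missing criterion for normal data are plain on the text and need no assumption. The switching of summaries is conditional: under visit-by-visit Shapiro–Wilk checks at 5%, n = 17 and correlation 0.5 to 0.8, it would affect about 25–30% of truly normal indicators and roughly 60–95% of log-normal ones at log-SD 0.3 to 0.8. It would make their descriptive time courses not comparable. Under a single judgement per indicator it would affect none.

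The error-rate effect is small: about 6% at most against the nominal 5%, only for comparisons of different people, and only if the smaller p is always the one reported.

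**What to change.** In section 2.5:

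1. Strike the rank-sum alternative from the sentence on normal data, so that the branches no longer share a test.
2. Replace the data-driven choice by one scale, one summary and one test for each indicator, or class of indicators, used at all seven visits and fixed before the data are seen. For example:
   - log scale with geometric means for concentrations expected to be right-skewed, such as ferritin, VEGF, IL-1β and the urinary microproteins;
   - raw scale for blood pressure, haemoglobin, FEV1 and walk distance;
   - median with a rank-based test for questionnaire scores.

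Mixed summaries then cannot occur, and a single pre-chosen test keeps the error rate of 10 v 7 comparisons near 5%.

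Cost: no data collection or procedure changes. The list must be drawn up in advance; sections 2.3.1 to 2.3.4 name many indicators, so working by class keeps this manageable. Some indicators will fit their pre-chosen scale imperfectly. The change does not settle whether tests across visits should be paired, which needs its own answer.

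### Section 2.5 names only independent-sample tests for quantitative indicators, although the central comparison is between seven measurements of the same 17 people

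*Protocol article*

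**What the plan says.** The Study population section (2.2) sets a single cohort: "The study will recruit 17 eligible medical professionals from Peking Union Medical College Hospital", 10 men and 7 women. No control or parallel group is described anywhere.

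The Design section (2.1) gives the purpose of the measurements, "to dynamically monitor the physiological and psychological acclimatization of medical professionals from Peking Union Medical College Hospital", and their schedule: "The monitoring will be conducted at seven key time points". These run from before departure, through the first week and four later points in Tibet, to the return to Beijing.

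Section 2.5, on the detection indicators, then names the tests. Normally distributed quantitative data "will be compared between groups with the use of Student’s t-test or the rank-sum test". For data that are non-normal or have unequal variances, "comparisons between groups will be performed by the Mann–Whitney U test". The threshold is "Two-tailed *p* < 0.05 is considered statistically significant".

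The article names no paired t-test, signed-rank test, repeated-measures analysis of variance, Friedman test or mixed model.

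**The concern.** With one cohort and no comparator, the question about acclimatization is how each person differs from their own pre-departure state. Both values in such a contrast come from the same individual and will usually be positively correlated. The rank-sum and Mann–Whitney tests, and a t-test between groups, assume that the two sets of values come from different people. Used on two visits, they leave stable differences between people in the error term, although those differences cancel when each person is compared with themselves.

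With positive correlation, standard errors come out too large and p values too high on average, so real changes may be missed. The article itself lists the sample of 17 as a limitation. Within-person comparison is the main feature of the design that offsets the small number, and the named tests do not use it.

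**Working it through.** **Inputs from the protocol article.** n = 17 (section 2.2; 10 + 7 = 17 agrees), seven time points (section 2.1), two-sided 0.05 (section 2.5). The article states no power, effect size, SD or within-person correlation, so there is no design figure to reproduce.

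**Assumptions, not in the article.** Two visits, 17 complete pairs, normal data with equal SD at both visits, true shift d in SD units (0.5, 0.8, 1.0), and within-person correlation r from 0 to 0.9.

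**Step 1: variance of a mean change.**
- True variance, paired: 2·SD²·(1−r)/17.
- Variance used by the independent test: 2·SD²/17.
- Ratio: 1/(1−r), which is 2.0 at r = 0.5, 3.3 at r = 0.7 and 10 at r = 0.9.

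**Step 2: interval width.** The standard-error ratio is 1/√(1−r): 1.414 at r = 0.5 and 3.162 at r = 0.9. Width also carries the t quantile, which is 2.037 on 32 df for the independent test and 2.120 on 16 df for the paired test.
- r = 0.5: 1.414 × 2.037/2.120 = 1.36.
- r = 0.9: 3.162 × 2.037/2.120 = 3.04.

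**Step 3: rejection rate when nothing changes.** Simulated rate of the independent t-test on paired data, nominal 5%:
- r = 0: 5.0%
- r = 0.3: 2.2%
- r = 0.5: 0.8%
- r = 0.7: 0.1%

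**Step 4: power.** Paired t-test: noncentral t on 16 df with noncentrality d·√17/√(2(1−r)). For d = 0.5 and r = 0.5 this is 0.5 × 4.123/1 = 2.06, giving 49%. The independent t-test figures are simulated on the same correlated data.

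| Shift (SD) | r | Independent t | Paired t |
|---|---|---|---|
| 0.5 | 0 | 29% | 28% |
| 0.5 | 0.3 | 26% | 37% |
| 0.5 | 0.5 | 23% | 49% |
| 0.5 | 0.7 | 19% | 70.5% |
| 0.8 | 0.5 | 66% | 87% |
| 0.8 | 0.7 | 70% | 98% |
| 1.0 | 0.5 | 88% | 97% |
| 1.0 | 0.7 | 92% | 99.9% |

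**Step 5: rank tests.** For a 0.5 SD shift, simulated power of Mann–Whitney against Wilcoxon signed-rank is 22% vs 47% at r = 0.5 and 17% vs 66% at r = 0.7. The non-normal route has the same weakness.

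**The case against.** The strongest reply is that section 2.5 never says the groups are visits. Between-person comparisons do exist: the cohort has men and women, and the Design section speaks of groups stratified on indicators. Two-sample tests suit those, and the name Student's t-test does not by itself exclude a paired version. On that reading the article only leaves the method for change over time to a fuller document.

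Part of this stands. Two-sample tests are legitimate for comparisons between different people, and the fix keeps them. But the strata in the Design section are formed to compare omics data, whereas section 2.5 covers the indicators themselves. Rank-sum and Mann–Whitney U are independent-sample tests under any reading. The section does choose tests, and none of the rank tests it chooses fits the main aim. An analysis plan that used signed-rank tests or a mixed model would depart from this text.

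The direction of the error also counts for the plan: with positive correlation it is conservative, so it tends to miss changes rather than invent them.

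A reader might go further and infer three things that the article does not support:
- **That most of the power is lost.** This depends on a correlation and an effect size that the article does not give. It is true of a 0.5 SD shift with r of about 0.5 or more, but not of large shifts or low correlation.
- **That real changes will be reported as non-significant.** Large changes would mostly still be detected, so the most that can be said is that they may be missed.
- **That the omics models share the fault.** Section 2.5 does not cover them. The section on leukocyte expression names software that can carry a participant term and states no model formula, so no wrong choice is fixed there.

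**Conclusion.** The point holds for the quantitative indicators in section 2.5. The article states tests that do not fit its central comparison, which is more than detail left out. If they are followed for visit-to-visit change, standard errors and p values are wrong wherever the within-person correlation is not zero.

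The loss is conditional. Under the assumptions above it exceeds half the power for a 0.5 SD shift once r reaches about 0.5. It is somewhat more than a quarter at 0.8 SD with r = 0.7 (70% against 98%) and under a tenth at 1.0 SD with r = 0.5 (88% against 97%). At r = 0 there is none. The practical risk is missed changes of small to moderate size. The correction is worth making before analysis because it is nearly free and the sample cannot easily be enlarged.

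**What to change.** In section 2.5, state that change over time in each quantitative indicator is analysed with a within-person method. One suitable form is a linear mixed model with visit as a seven-level fixed factor and participant as a random effect, or with a repeated-measures covariance structure, and with planned contrasts of each later visit against pre-departure. For simple two-visit comparisons, name the paired t-test, with the Wilcoxon signed-rank test for non-normal data. Restrict Student's two-sample t-test and the Mann–Whitney U test to comparisons between different people.

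The cost is a few sentences and the analysis syntax. The named software, SPSS 26, already fits mixed models, and no new data, visits or participants are needed.

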In the present study, we aim to integrate the multi-omics sequencing outcomes obtained at seven distinct temporal intervals with the fluctuations observed in a array of biomarkers at corresponding time points. The objective is to delineate small molecules that are intrinsically linked to high-altitude acclimatization and to investigate the underlying molecular pathways. Concurrently, we propose to conduct a comparative analysis of omics sequencing data from groups stratified based on varying detection indicators across different time points. This approach is intended to elucidate the molecular mechanisms that may underpin the disparities in detection indicators. It is anticipated that these analytical endeavors will contribute to a more nuanced comprehension of altitude-induced illness and the physiological processes associated with altitude acclimatization. The trial design is presented in Figure 1, while the subsequent sections provide a comprehensive and detailed description of our trial.

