#### Subjective assessments

2.3.3

Subjective assessments are conducted using the Lake Louise Acute Mountain Sickness Symptom Rating Scale to gauge the incidence of acute mountain sickness among the medical support staff in Tibet (15). The Adult Self-rating Health Scale is employed to evaluate scores for anxiety, depression, hostility, and somatization symptoms (16). The Pittsburgh Sleep Quality Index is utilized to assess alterations in subjective sleep quality (17). The Depression-Anxiety-Stress Scale is used to gauge the emotional state of the Tibetan medical professionals (18). Additionally, a questionnaire survey is conducted to evaluate the perception of oxygenation, oxygen comfort, thermal sensation, and thermal comfort under various experimental conditions (19).

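### Section 2.5 names only independent-sample tests for 17 people measured seven times: chi-square has no exact or paired alternative, and unequal variance leads to Mann–Whitney

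*Protocol article*

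**What the plan says.** Section 2.2 of the protocol article fixes the sample: "The study will recruit 17 eligible medical professionals from Peking Union Medical College Hospital". The split by sex is set in advance at 10 men and 7 women. Section 2.1 makes it a repeated-measures cohort: "The monitoring will be conducted at seven key time points". The same section plans comparisons inside the cohort, a "comparative analysis of omics sequencing data from groups stratified based on varying detection indicators across different time points", without giving group sizes.

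Section 2.5 then sets the tests for the detection indicators:

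- Categorical data: "Enumeration data will be presented as ratios and percentages, and χ^2^ tests will be used for comparison". No small-sample or paired alternative is named.
- Quantitative data failing either of two conditions: "Quantitative data that do not follow a normal distribution or homogeneity of variance will be presented as median and IQR". The test prescribed for such data is Mann–Whitney, so unequal variance alone is enough to trigger it.
- Normally distributed data: Student's t-test or the rank-sum test, with no rule for choosing between them.

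Significance is two-sided at 0.05. Binary indicators include acute mountain sickness, where section 2.3.3 uses the Lake Louise scale "to gauge the incidence of acute mountain sickness among the medical support staff in Tibet", and fundus edema and hemorrhage (section 2.3.2).

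**The concern.** Two kinds of comparison are possible in this study, and the stated tests suit neither well. Comparisons between people split a group of 17, which is too small for the chi-square approximation to be taken on trust. Comparisons between visits use the same people twice, which chi-square, the rank-sum test and Mann–Whitney all ignore.

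Mann–Whitney is also not a remedy for unequal spread if the question is whether one group is higher than the other. Finally, for two independent groups the rank-sum test is the Mann–Whitney test. Allowing it for normal data removes the distinction that the next sentence draws and leaves the choice open until both p values are known.

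At stake is whether a reported p value below or above 0.05 can be relied on, in a study where a handful of events decides each binary comparison.

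**Working it through.** The article gives no power or error-rate figure to reproduce. Inputs from it are n = 17, the 10/7 split by sex, seven time points and two-sided 0.05. SD ratios, within-person correlations and other splits are assumptions, since the article states none.

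**1. Expected counts, tables between people.** The four expected counts of a 2x2 table sum to N, so four values of at least 5 need N ≥ 20. With N = 17, the smallest expected count is (smaller row total × smaller column total)/17. Its largest possible value is 8 × 8/17 = 3.76. For 10 against 7 it is 7 × 8/17 = 3.29.

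Example, 0/10 against 3/7:
- Pearson: 17 × (0 × 4 − 10 × 3)² / (10 × 7 × 3 × 14) = 15,300/2,940 = 5.20, p = 0.023.
- Fisher: C(7,3)/C(17,3) = 35/680 = 0.051.

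Pearson and Fisher fall on different sides of 0.05 in 6 of the 88 possible 10-against-7 tables.

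**2. Expected counts, tables between visits.** Chi-square would compare 17 with 17. With T events in total, the expected counts are T/2 and (34 − T)/2, so all are at least 5 when T is 10 to 24. The condition can be met here; the fault is the ignored pairing.

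**3. Chi-square against McNemar.** For 0/17 against k/17 there are k discordant pairs, all in one direction. Exact McNemar is 2 × 0.5^k, and mid-p is half of that.

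| k | Pearson, uncorrected | Exact McNemar | Mid-p McNemar |
|---|---|---|---|
| 4 | 0.033 | 0.125 | 0.063 |
| 5 | 0.015 | 0.063 | 0.031 |
| 6 | 0.007 | 0.031 | 0.016 |

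For k = 4, Pearson is 34 × (17 × 4)² / (17 × 17 × 4 × 30) = 157,216/34,680 = 4.53.

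Over all 1,140 possible paired tables with n = 17, uncorrected Pearson is below 0.05 while exact McNemar is not in 120, and the reverse never occurs. Of these 120, 100 satisfy the expected-count condition and 54 disappear if mid-p McNemar is the comparator.

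**4. True type I error of uncorrected chi-square.**
- Independent groups: at most 5.3% (10 against 7), 5.2% (8 against 9) and 5.8% (17 against 17).
- Paired visits, exact enumeration over event rates of 5% to 95%: at most 5.8% at within-person correlation 0, 4.5% at 0.1, 2.3% at 0.3 and 0.8% at 0.5.

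**5. Mann–Whitney under unequal variance.** Simulation: 20,000 runs, normal data, equal centres, threefold SD ratio.

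| Split | Smaller group more variable | Larger group more variable |
|---|---|---|
| 10 / 7 | 7.9% | 4.3% |
| 12 / 5 | 9.8% | 2.3% |
| 13 / 4 | 12.3% | 1.1% |

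Welch's t-test gave 4.8% to 5.8% throughout. Simulation error is about ±0.4 percentage points at 8%. With equal SDs at 10 against 7, Mann–Whitney gave about 4.3%.

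**The case against.** The strongest reply is that little of this inflates error. A reader might infer that chi-square can never meet its condition in this study, or that it will produce false positives between visits. Neither follows. The condition is out of reach only for tables between people; between visits it is often met, and most disagreements with exact McNemar arise where it is met. For independent groups the true error stays at or below 5.8%, and with positively correlated visits it falls well below 5%, so the general cost is lost power.

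The disagreements also depend on the comparator. Exact McNemar cannot reach 0.05 with fewer than six discordant pairs. Under mid-p, the k = 5 example is significant by both tests; k = 4 still differs.

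The use of chi-square between visits is an inference. Section 2.5 does not say what it will compare, and section 2.3.3 describes incidence without naming a test. Student's t-test could also be run in its paired form, although the text speaks of comparisons between groups.

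On Mann–Whitney, the SD ratio and the 12/5 and 13/4 splits are assumed. The test remains valid for identical distributions, and it is milder than pooled Student's t in the bad direction (10.2% at 10 against 7). The article also admits that the small sample limits robustness (sections 3 and 5).

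All of this limits the size of the problem. It does not supply the missing paired or exact option, make unequal variance a sound trigger for Mann–Whitney, or settle which test applies to normal data. An unseen analysis plan would have to overrule what section 2.5 states, not merely add to it.

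**Conclusion.** The point holds in four parts.

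- **Between people:** the expected-count condition is unattainable in 2x2 tables, and some conclusions differ from Fisher's test. This follows from n = 17 alone.
- **Between visits:** if chi-square is used there, its p values are wrong because pairing is ignored. It is conservative under positive correlation, yet gives a smaller p value than either form of McNemar for a few new events from a zero baseline, such as 0/17 against 4/17. Such baselines are plausible in healthy participants, but the article does not state them.
- **Unequal variance:** as a test of location, Mann–Whitney departs moderately from 5% at 10 against 7 and more at less equal splits. The size depends on the assumed threefold SD ratio and on which group is more variable.
- **Normal data:** two tests are left open for the same data.

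The change is worth making because it is specific and nearly free. The documents do not support a claim that the study's binary results will generally be false positives.

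**What to change.** Revise section 2.5 as follows:

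- Binary indicators at two visits: McNemar's test, with exact or mid-p chosen in advance. Several visits: Cochran's Q with an exact or permutation p value.
- Binary indicators between groups of people: Fisher's exact test, or its mid-p form if chosen in advance.
- Quantitative indicators between groups: Welch's t-test when variances are unequal. Keep Mann–Whitney for non-normal data only.
- Normal data: delete the rank-sum option.
- State for each test whether it compares groups of people or visits.

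This costs a few sentences and uses standard methods. The downside is somewhat larger p values for rare binary findings, most of all with the exact forms.
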